### 9.2.2 Cost analysis

All health-care resources will be converted into cost estimates by multiplying the number of health-care units use by standard unit prices. The cost analysis will be performed by using a business case model. The economic analysis will estimate the value for money afforded by the remote eCTG monitoring Home monitoring compared to conventional In-Hospital CTG monitoring (ward/outpatient clinic). The cost of the antenatal care will be calculated following description in section 7.1.2 and Table 27.1.2. All results will be reported as mean, median and percentage (%). A sub-analysis will be presented of a home monitoring patients journey versus in-hospital and a home patients journey versus outpatient clinic patients journey.

*Table 2: Cost analysis supposing antenatal Home monitoring versus In-Hospital monitoring (Ward, outpatient clinic) based on patients journey of the HASTA Home@Hospital population.*

| Antenatal care Costs                            | Home patients journey costs (N=60) |                  |             | In-Hospital patients journey costs (N=60) |                  |             | Difference     |
|-------------------------------------------------|------------------------------------|------------------|-------------|-------------------------------------------|------------------|-------------|----------------|
|                                                 | Mean costs (€)                     | Median costs (€) | Treated (%) | Mean costs (€)                            | Median costs (€) | Treated (%) | Mean costs (€) |
| Home monitoring (admission day)                 |                                    |                  |             | -                                         | -                | 0%          |                |
| In-Hospital (admission day)                     |                                    |                  |             |                                           |                  |             |                |
| Remote eCTG                                     |                                    |                  |             | -                                         | -                | 0%          |                |
| Conventional CTG Outpatient clinic              |                                    |                  |             | -                                         | -                | 0%          |                |
| Conventional CTG Ward                           |                                    |                  |             |                                           |                  |             |                |
| Emergency transport                             |                                    |                  |             | -                                         | -                | 0%          |                |
| Visit outpatient clinic (scheduled)             |                                    |                  |             | -                                         | -                | 0%          |                |
| Visit outpatient clinic (unscheduled/emergency) |                                    |                  |             | -                                         | -                | 0%          |                |
| Total costs                                     |                                    |                  |             |                                           |                  |             |                |

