### ***Costs supposing antenatal home monitoring versus in-hospital monitoring (ward, outpatient clinic).***

To assess the costs of remote home monitoring versus in-hospital monitoring, patient journeys will be followed and costs calculated as if they were at home using remote eCTG compared to in- hospital using conventional CTG. The patient journey will not depend on participation in the HASTA study but is part of the standard care. Total of costs (mean and median) and the percentage of patients with at least one registered activity (% treated). In addition, a sub-analysis will be presented of participants needing hospitalization and of participants monitoring at the outpatient clinic at inclusion. Potential patient journey are shown in Figure 11.

Overview of cost analysis is presented in Table 2. The upper blue panel presents the population with indication to be monitored in-hospital. The patients' journey is presented by green circles (home monitoring) compared to the blue circles (in-hospital monitoring). The yellow circles in this panel presents the weekly scheduled visits at the outpatient clinic (standard care).

The lower yellow panel presents the population with indication to be monitored at the outpatient clinic. The patients' journey is presented by green circles (home monitoring), compared to the yellow circles (outpatient clinic monitoring) and/or blue circles (in-hospital monitoring). Every circle presents a day and the arrows presents the possible shifts during the patients' journey. For example, when hospitalization is indicated for a patient – initially monitored at the outpatient clinic – a shift to the blue line will take place. In some more exceptional cases, a patient – initially monitored in-hospital – can be discharged and will receive monitoring at the outpatient clinic. In that case, a shift to the yellow line will take place.

[figure not shown]

Figure 11. Patients Journey of Home versus In-Hospital monitoring (blue upper panel); Patients Journey Home versus Outpatient clinic monitoring (yellow lower panel).

Potential cost components in a “Patients Journey Home monitoring” versus “In-Hospital admission”:

- Costs (euros) of Home admission.
  - Including total of consult(s) by telephone and use Luscii® app.
  - Based on total costs per patient (mean/median).
- Costs (euros) of remote eCTG during Home admission.
  - Based on costs total of eCTG measurements (30-90 minutes) per patient (mean/median).

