- Costs (euros) of emergency ambulance transport (if needed).
  - Based on costs total of ambulance transport per patient (mean/median).
- Costs (euros) of unscheduled Outpatient clinic visits.

- Based on costs total of additional visits (emergency) at the outpatient clinic per patient (mean/median).
- Costs (euros) of weekly scheduled Outpatient clinic visits.
  - Based on costs total of planned visits at the outpatient clinic once a week per patient (mean/median).
- Costs (euros) of the In-Hospital admission.
  - Based on costs total number of admission days per patient in case hospitalization is needed (mean/median).
- Costs (euros) of conventional CTG during In-Hospital admission.
  - Based on costs total number of conventional CTG measurements per patient in case hospitalization is needed (mean/median).

*Potential cost components in a “Patients Journey Home monitoring” versus “Outpatient clinic monitoring”:*

- Costs (euros) of Home monitoring ( $\geq 2x/\text{week}$ ).
  - Including total of consult(s) by telephone and use Luscii® app.
  - Based on total costs per patient (mean/median).
- Costs (euros) of remote eCTG during Home monitoring ( $\geq 2x/\text{week}$ ).
  - Based on costs total of eCTG measurements (30-90 minutes) per patient (mean/median).
- Costs (euros) of emergency ambulance transport.
  - Based on costs total of ambulance transport per patient (mean/median).
- Costs (euros) of unscheduled outpatient clinic visits.
  - Based on costs total of additional visits (emergency) at the outpatient clinic per patient (mean/median).
- Costs (euros) of weekly scheduled outpatient clinic visits.
  - Based on costs total of planned visits at the outpatient clinic once a week per patient (mean/median).
- Costs (euros) of conventional CTG measurement (30-90 minutes) et the Outpatient clinic ( $\geq 2x/\text{week}$ ).
  - Based on costs conventional CTG measurements at the Outpatient clinic per patient (mean/median).
- Costs (euros) of the In-Hospital admission.
  - Based on costs total number of admission days per patient in case hospitalization is needed (mean/median).
- Costs (euros) of conventional CTG during In-Hospital admission.
  - Based on costs number of conventional CTG measurements per patient in case hospitalization is needed (mean/median).

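### Table 2 presets the comparator's outpatient CTGs and clinic visits to 0% for all 60 women, contradicting its own title and section 7.1.2

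*Protocol*

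**What the plan says.** Protocol section 9.2.2 sets the home journey "compared to conventional In-Hospital CTG monitoring (ward/outpatient clinic". Table 2 carries the same scope in its title: "Cost analysis supposing antenatal Home monitoring versus In-Hospital monitoring (Ward, outpatient clinic". Its comparator columns are headed "In-Hospital patients journey costs (N=60", so they cover the whole cohort.

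In those columns a dash for the mean, a dash for the median and 0% treated are already entered for home monitoring, remote eCTG, "Conventional CTG Outpatient clinic", emergency transport, "Visit outpatient clinic (scheduled" and the unscheduled clinic visit. The rows left open are ward admission days, ward CTG and the total.

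Section 7.1.2 describes two populations. For women with an indication for clinic monitoring it states: "The patients' journey is presented by green circles (home monitoring), compared to the yellow circles (outpatient clinic monitoring) and/or blue circles (in-hospital monitoring". Its component list for the home-versus-outpatient comparison includes conventional CTG at the clinic at least twice weekly, "Based on costs conventional CTG measurements at the Outpatient clinic per patient (mean/median", together with weekly planned visits and unscheduled visits. It also allows a woman who starts on the ward to move, exceptionally, to clinic monitoring. Section 7.3.1 identifies eligible women both at admission and at the outpatient clinic, and section 7.3.2 gives outpatients their own procedures.

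**The concern.** The shell fits women whose usual care is on the ward but carries the N of the whole cohort. A woman followed only at the clinic has entries to fill in the home columns. In the comparator columns every row that could hold her usual care is preset to nothing, so she enters at zero cost and her row-by-row difference makes home monitoring look like pure added cost. Averaged over 60 women, this pulls the comparator mean down and makes home monitoring look less favourable than the protocol's own costing method would show.

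Costs are a named secondary outcome, and section 9.2.2 presents the analysis as an estimate of value for money. The N=60 table is where a reader will look for that result.

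**Working it through.** **Inputs from the protocol.** Comparator N = 60 (Table 2). Treated % is the share of patients with one or more recorded uses of the item (section 7.1.2). Clinic CTG occurs at least 2 times per week and planned visits once per week (section 7.1.2).

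**Not given.** The number of women k whose usual care includes the clinic, the mean weeks w they spend there, and the unit prices. I vary k from 0 to 60 and w from 1 to 5 as assumptions; the entry window of 32+0 to 36+6 weeks spans five weeks.

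**Step 1: can the printed 0% be reproduced?** Treated % for clinic CTG = 100 × k/60. This equals 0 only when k = 0. A single outpatient gives 100 × 1/60 = 1.7%. Since the protocol enrols women at the clinic, the printed value does not follow from its design.

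**Step 2: what is left out of the comparator mean?** Clinic CTGs omitted per woman, averaged over 60, are at least k × 2 × w/60. Planned visits omitted are k × w/60, half as many.

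| k | Treated % | CTGs omitted, w = 1 | w = 2 | w = 5 |
|---|---|---|---|---|
| 0 | 0 | 0 | 0 | 0 |
| 1 | 1.7 | 0.03 | 0.07 | 0.17 |
| 6 | 10.0 | 0.20 | 0.40 | 1.00 |
| 12 | 20.0 | 0.40 | 0.80 | 2.00 |
| 20 | 33.3 | 0.67 | 1.33 | 3.33 |
| 30 | 50.0 | 1.00 | 2.00 | 5.00 |
| 60 | 100.0 | 2.00 | 4.00 | 10.00 |

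Example: k = 20, w = 2 gives 20 × 2 × 2/60 = 1.33 CTGs and 20 × 2/60 = 0.67 visits. These rows illustrate how the omission scales; they do not predict its size.

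**Step 3: in euros.** The understatement of the comparator mean is at least (k/60) × (2w × CTG price + w × visit price), plus any unscheduled visits. With k, w and both prices unknown, no euro figure can be given. The direction is fixed: for any k above zero the comparator is too low.

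**Step 4: row by row.**
- Home monitoring and remote eCTG: 0% in the comparator is correct.
- Clinic CTG: 0% contradicts section 7.1.2 directly, because conventional CTG at the clinic is usual care for outpatients.
- Scheduled visits: 0% cannot hold for women whose usual care takes place at the clinic, and weekly visits are a listed component.
- Unscheduled visits: also a listed component of the home-versus-outpatient comparison. The list does not assign it to an arm, so the contradiction is less direct, but a preset 0% rules such visits out before the journeys are followed.
- Emergency transport: listed in the comparison, but section 7.1.2 does not say that it arises in usual care. The entry is unclear and not shown to be wrong.

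**The case against.** The strongest defence is that Table 2 is an empty reporting shell and that section 7.1.2 already sets out the right method: outpatients have their own panel, their own comparator and the relevant components. On that view the result goes wrong only if the shell is followed over the text. This is fair as to consequence, but it does not remove the conflict. Section 9.2.2 sends the analyst to both section 7.1.2 and the table, gives neither precedence, and the table states values that section 7.1.2 excludes. The pattern of dashes is consistent across rows, so it is unlikely to be an extraction fault.

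A second defence is the planned sub-analysis of home versus in-hospital and home versus outpatient clinic. It would expose the missing costs, which limits the harm, but it does not correct the N=60 columns. A reader might infer that the sub-analysis is itself defective because Table 2 cannot display it. The protocol does not say that Table 2 must display it, and separate shells may sit in the SAP.

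A reader might also infer that outpatients will be costed as if admitted, which would inflate the saving. Nothing in the protocol says so; section 7.1.2 gives them a separate path. Likewise, the absence of an interval around the mean difference is no error here: the protocol plans a descriptive business-case summary, and interval methods can be left to the SAP.

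**Conclusion.** The point holds as an internal contradiction in a table shell. For outpatient conventional CTG and scheduled clinic visits, and less directly for unscheduled visits, the preset 0% in the N=60 comparator conflicts with the table's title, the text of section 9.2.2 and section 7.1.2. It is right only if no woman's usual care includes the clinic. Completed as printed, the table understates comparator cost.

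The size is unknown. It depends on an outpatient share, a duration and unit prices that the protocol does not give, so any specific count of missing CTGs or visits would be an assumption and not a minimum. It would also go too far to call the planned cost comparison wrong as a whole, or to count the emergency-transport row as an error. Costs are a secondary outcome in a single-arm feasibility study; the primary outcome and the sample size of 60 are unaffected.

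**What to change.** Either of two changes resolves it:

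- Open the comparator cells for outpatient conventional CTG and for scheduled and unscheduled clinic visits, and fill them from each woman's own standard-care path, as section 7.1.2 describes.
- Keep the present shell for the in-hospital stratum only, with that stratum's own N, and add a matching home-versus-outpatient table with its N and a total. The clinic rows of the in-hospital table should still accept entries for women who are discharged to clinic monitoring.

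In both cases, confirm whether 0% for emergency transport is intended to apply to outpatients. Also state which text governs if section 7.1.2 and Table 2 differ.

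The cost is a revised table shell. Section 7.1.2 already plans to follow the patient journeys and count the units, so no new data collection is needed.

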### 9.3 Additional measurements

Other study parameters - measurement fetal and maternal heartrate, Doppler umbilical and uterine artery ([images removed])

*Figure 3* - will be analyzed by technical PhD students in collaboration with the TU/e with the aim to test the feasibility of these simultaneous measurements as a first step towards the development of a prediction model. The data collected through the additional measurements will be used to test if maternal-fetal coupling patterns change in cardio-vascular high- versus low-risk pregnancies. Also, the variability of the coupling parameters within the two groups will be evaluated. The Partial Directed Coherence (PDC) method will be used on simultaneously recorded fetal and maternal beat-by-beat heart rates collected from fetal and maternal eCTG signals, and on umbilical and uterine arteries parameters recorded from US signals of cardio-vascular high- (n=12) and low-risk (n=12)

pregnancies. The PDC fetal-to-maternal coupling analyses will provide information about the directionality and the magnitude of the cardiovascular coupling considering fetus-to-mother coupling (A\_fBBI→ mBBI) and mother-to-fetus coupling (A\_mBBI→ fBBI). Furthermore, this analysis will investigate how these coupling relationships can be mediated and influenced by the placenta (37).

The additional measurements are integrated into the HASTA protocol in the context of scientific collaboration between the MMC and the TU/e. As the HASTA study population exactly matches the population aimed for the measurements and analyses that the PhD students involved intend to perform. By integrating these measurements into the HASTA study, patients, healthcare personnel and the MMC research team are not unnecessarily burdened with a separate study for a few measurements. HASTA participants are informed in the PIF about the additional measurements and can choose to participate or not.

Measurement of FHR exported from the eCTG monitor collected in this study, will be analyzed by technical PhD student in collaboration with the TU/e – aiming to define the FHR profile of a healthy fetus and develop an automated interpretation of the fetal ECG measurement obtained from the eCTG measurements. The eCTG data collected in the HASTA study will be used to check if the algorithm of the FHR – developed during labor – can also benefit for premature fetus. If not, to define what steps are needed for further developments. Data will be analyzed by using a positive predictive metric for estimating sensitivity (Se), specificity (Sp) and positive predictive values (PPV). Results will be described in percentages (%) using Se, Sp, PPV (*p*-value) and their 95% confidence intervals (95% CI). All analyses will be done in collaboration with the clinical team, with the purpose to contribute to improve (future) pregnancy outcomes (section 11.6).

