**Study population:** Pregnant patients (N=60) >18 years old with a singleton, high-risk pregnancy from 32 until 37 weeks of gestational age. High-risk is defined as: diagnosed with PE, FGR, PPRM, or others with an indication for fetal monitoring at least twice a week, these patients are eligible for inclusion in this study. The main exclusion criteria are: suspected labor within 48 hours, severe pre-eclampsia, umbilical artery Doppler with absent- or reversed flow, external- or implanted electrical stimulator and language barrier.

**Intervention:** Remote eCTG monitoring (using Nemo Remote®), daily in a Home@Hospital setting for 30-90 minutes, or at least twice weekly at the outpatient clinic. Monitoring duration depends on signal quality and interpretability of the eCTG tracing, and lasts at least 30 minutes, and will be ceased after 90 minutes if the eCTG signal quality and/or interpretability is then still insufficient. In 24 patients ultrasound clips of 2 x 5 minutes of the uterine and umbilical artery Doppler will be collected simultaneously to the eCTG measurements.

**Main study parameters/endpoints:** Primary outcome: The percentage of successful eCTG measurements in a Home@Hospital setting. This will be defined as the necessity to switch to conventional CTG based on the amount of signal loss. Secondary outcomes: Automated interpretation of the eCTG, maternal and perinatal outcomes, patient and healthcare professional satisfaction and costs. Additional outcome: Feasibility of synchronized multimodal acquisitions of maternal and fetal measurements.

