### 4.3 Exclusion criteria

A potential subject who meets any of the following criteria will be excluded from participation in this study:

- An indication for intravenous medication
- Blood pressure >160/110mmHg
- Absent-/or reversed flow umbilical artery Doppler
- HELLP (Table 1)
- Obstetric intervention expected <48 hours, e.g. due to:
  - Non reassuring CTG
  - Active vaginal blood loss
  - Signs of abruption placentae
  - Meconium stained amniotic fluid
  - Signs of chorioamnionitis
- Patients admitted with a clinical diagnosis of sepsis with hypotension (i.e. septic shock).
- Insufficient knowledge of Dutch or English language
- Insufficient comprehension of instruction Nemo Remote® or patient information
- Fetal and/or maternal cardiac arrhythmias
- Contraindications to abdominal patch placement (dermatologic diseases of the abdomen precluding preparation of the abdomen with abrasive paper)
- Patients connected to an external or implanted electrical stimulator, such as Transcutaneous Electro Neuro Stimulation (TENS) and pacemaker (because of disturbance of the electrophysiological signal).

*Table 1. Definitions of pregnancy related diagnosis*

|                                                                                                                                                                                                                                                                                                                                                                                                                                                                                                                                                                                                                                                                                                                                                                                                                                                                                                                                                                                                                                                                           |

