#### **4.4 Sample size calculation**

In a previous cohort study for conventional remote CTG monitoring, 4% of all tracings needed repetition (562 out of 12,649) and 0.9% (N=111) of the CTGs had to be repeated in the hospital. The success rate at first trace was 95.5% and after repetition 99% (28) .

A success rate of 90% is considered clinically sufficient based on previous studies (28-30) and HCPs' opinion. Only the first day of remote eCTG measurements will be used for determination of the feasibility by assessing the signal quality and success. If the remote eCTG measurement is technically insufficient but reassuring – according to current clinical policy – it can be repeated once at the same day and still be considered successful. Calculated on 90% chance of success according Wilson standard error of proportions (CI95% > lower limit of 82.5%), 60 subjects are needed for inclusion in this cohort study.

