### 5.1 Investigational treatment

All patients will receive routine care following national guidelines and/or local protocols. Participants at the clinic will receive self-administered remote eCTG monitoring by NRM once a day (*Figure 1*). In case of follow-up at the outpatient clinic, participants will receive self-administered remote eCTG monitoring by NRM once per day or at least twice a week, depending on their care path. The realtime eCTG measurement will be instantly transferred digitally to the hospital electronic patient file (Chipsoft HiX) and assessed real-time on interpretability by the HCP. Monitoring will last between 30-90 minutes depending on the interpretability and reassurance of the remote eCTG measurement. Criteria defining a successful measurement are described in a standard operating procedure (SOP) and will be available for HCPs at the hospital to avoid prematurely closing of the eCTG measurement (see section 7.1.1). All HCPs involved in this study will receive training on the study protocol. The study procedure and statistical analysis are described in section 7.3.2, chapter 9 and in *Figure 12*.

Monitoring will be repeated the same day when reassuring but insufficiently interpretable, or upon request of the HCP in case of concerns about maternal and/or fetal condition. Additional detailed information of the NRM is described under investigational product (chapter 6). When remote eCTG interpretability is insufficient – based on clinical assessment of HCPs – a switch to conventional CTG monitoring will take place. In this study, HCPs will be asked to define clearly if a switch to conventional CTG was made based on insufficient interpretability or because of concerns about fetal and/or maternal condition (section 7.1.2).

From the second day onward, synchronized US Doppler measurements (clips of 2 x 5 minutes) of the umbilical and uterine arteries will be performed simultaneously with the remote eCTG for 24 patients ([images removed]

*Figure 3*). Measurements of two groups - cardiovascular low (PPROM; N=12) versus cardiovascular high-risk (PE/FGR; N=12) - will be collected and analyzed to evaluate the feasibility of synchronized multimodal acquisitions of maternal and fetal measurements.

[images removed]

*Figure 3. Measurement fetal and maternal heartrate, Doppler arteria umbilicalis, Doppler uterine artery and uterine activity.*

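### Section 9.3 promises a healthy-fetus FHR profile from a cohort that is entirely high-risk, and Se and PPV from it are likely to be imprecise and cohort-specific

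*Protocol*

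**What the plan says.** Section 9.3 (Additional measurements) states the purpose of the FHR export as "aiming to define the FHR profile of a healthy fetus and develop an automated interpretation of the fetal ECG measurement". The same paragraph asks whether an algorithm built on labour data is of use in the premature fetus and, if not, what further development is needed. The planned measures are "estimating sensitivity (Se), specificity (Sp) and positive predictive values (PPV", reported as percentages with a 95% CI and a p-value.

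The Summary describes the population as women "with a singleton, high-risk pregnancy from 32 until 37 weeks of gestational age" and adds: "High-risk is defined as: diagnosed with PE, FGR, PPRM, or others with an indication for fetal monitoring at least twice a week". Section 4.2 sets the same entry condition. The design is a single cohort with no low-risk or healthy comparison group.

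Section 4.3 excludes "Absent-/or reversed flow umbilical artery Doppler", fetal arrhythmia, and women in whom an obstetric intervention is expected within 48 hours. A non-reassuring CTG is one of the example reasons for that last criterion.

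Under section 7.3.2, recording goes on after inclusion until the woman goes home, delivers or gets to 37 weeks. Section 5.1 asks staff to record whether "a switch to conventional CTG was made based on insufficient interpretability or because of concerns about fetal and/or maternal condition".

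**The concern.** A reference profile takes its meaning from the population behind it. If the FHR pattern of fetuses in PE, FGR and PPROM pregnancies is labelled healthy, any algorithm that uses it as its normal range inherits a range learned from complicated pregnancies. A later user has no way to see this from the label.

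The second part concerns the accuracy measures. Sensitivity is estimated only from affected records, and PPV depends strongly on how common they are. The entry criteria take out some of the fetuses most likely to be affected. What is left may contain few of them, so the two measures could look like properties of the algorithm when they mainly reflect who was admitted to the study.

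**Working it through.** **Profile: the texts side by side.** Section 9.3 names a healthy fetus as the object of the profile. The Summary and section 4.2 admit only women with an indication for monitoring at least twice weekly. Section 5.1 calls PPROM low-risk in the cardiovascular sense, but only to form the two groups of 12 in the Doppler subset; the Summary still counts PPROM as high-risk. Section 9.3 gives no rule for selecting healthy fetuses from the cohort. Followed as written, the profile would be drawn from high-risk pregnancies and carry a healthy label.

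**The plan's own figure.** The protocol states no sample size, prevalence or precision for the automated-interpretation work. Its only figure is in section 4.4, "60 subjects are needed for inclusion in this cohort study", set for the primary success rate.
- Wilson, the method named there, with 54/60 and z = 1.96: (0.9 + z²/120 ± z·√(0.09/60 + z²/14400)) / (1 + z²/60) gives 79.9% to 95.3%, which does not reach the stated lower limit of 82.5%.
- Normal approximation: 0.9 − 1.96·√(0.09/60) = 82.4%, close to the stated limit.

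That mismatch is a separate matter. Here 60 is taken as given.

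**Precision at N = 60.** Inputs: N = 60 from section 4.4. Assumed, because the protocol gives none of them: 3 to 18 affected fetuses (5% to 30%), Se about 80%, Sp about 90%, and one fetus-level record per woman.

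For k affected:
- true positives = 0.8k, rounded
- true negatives = 0.9(60 − k), rounded
- false positives = (60 − k) − true negatives
- PPV = true positives / (true + false positives)
- exact (Clopper-Pearson) 95% limits for x/n: the 2.5% quantile of Beta(x, n − x + 1) and the 97.5% quantile of Beta(x + 1, n − x)

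| Affected (k) | Se (95% CI) | Sp (95% CI) | PPV (95% CI) |
|---|---|---|---|
| 3 (5%) | 2/3 (9-99%) | 51/57 (79-96%) | 2/8 (3-65%) |
| 6 (10%) | 5/6 (36-99.6%) | 49/54 (80-97%) | 5/10 (19-81%) |
| 12 (20%) | 10/12 (52-98%) | 43/48 (77-97%) | 10/15 (38-88%) |
| 18 (30%) | 14/18 (52-94%) | 38/42 (77-97%) | 14/18 (52-94%) |

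The sensitivity interval is about 90 points wide with 3 affected (99.2 − 9.4) and still about 41 with 18 (93.6 − 52.4). Specificity is better supported throughout.

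**Dependence of PPV on the case mix.** PPV = Se·p / (Se·p + (1 − Sp)(1 − p)). With Se 0.8 and Sp 0.9:
- p = 0.05: 0.040/(0.040 + 0.095) = 30%
- p = 0.10: 0.080/(0.080 + 0.090) = 47%
- p = 0.30: 0.240/(0.240 + 0.070) = 77%

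The same algorithm gives very different PPVs depending only on who is enrolled.

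**The case against.** A reader might infer that neither a healthy profile nor Se and PPV can be obtained at all. The documents do not support that.

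- **Profile.** A high-risk pregnancy is not an unhealthy fetus. FGR is any estimated weight or abdominal circumference below the 10th percentile (Table 1), and other indications may enter. Apgar score, cord pH and mortality are collected (section 7.1.2), so fetuses with reassuring tracings and normal outcome can be picked out afterwards. This stands, and the fix relies on it. It does not rescue the label, because such fetuses still come from complicated pregnancies.
- **Computability.** Sensitivity exists once there is one affected record, and PPV once the algorithm flags one. The difficulty is precision and reach.
- **Entry filter.** Section 4.3 does not exclude non-reassuring tracings as such; the criterion is an intervention expected within 48 hours. Abnormal tracings can occur after inclusion.
- **Recording under concern.** One might infer that eCTG stops as soon as the fetus deteriorates. Section 5.1 also provides for repeat monitoring on request when there is concern, and concern-driven switches to conventional CTG are logged.
- **Birth outcome as truth.** Section 9.3 names no reference standard, so it cannot be faulted for using birth outcome as one. The target condition, reference standard and unit of analysis may sit in an analysis plan that is not at hand, and their absence is not held against the protocol.
- **Number affected.** If the target is a feature of a tracing or an event, positives could be numerous, since inpatients are recorded daily. Repeated tracings from one woman are not independent, however, and add less than their number suggests.
- **Weight.** Section 9.3 already requires 95% CIs, which would show the imprecision, and its aim of checking whether the algorithm carries over is modest. This is a good reason to keep Se and PPV.

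**Conclusion.** The mismatch between the healthy-fetus aim and the all-high-risk cohort holds on the text alone and needs no assumption. The second part is conditional. If the target is a fetus-level condition, Se and PPV are likely to be imprecise and to describe only this selected cohort. Its size rests on the assumed 3 to 18 affected of 60, one record per woman, Se near 80% and Sp near 90%. On those assumptions the exact 95% CI for sensitivity runs from 9-99% to 52-94%.

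The p-value in section 9.3 has no stated null value, so it tests nothing that a reader could name.

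The matter is confined to the automated-interpretation work, which the protocol lists under both secondary (section 2.2) and additional (section 2.3) objectives. The primary outcome and its sample size are not affected.

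**What to change.** In section 9.3:

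1. Replace the healthy-fetus aim with: *FHR profile of reassuring tracings from fetuses with normal outcome in high-risk pregnancies at 32-37 weeks*. Restrict the profile to those tracings, and say which of the outcomes already collected under section 7.1.2 count as normal.
2. Show the profile by indication: PE, FGR, PPROM, other.
3. Keep Se, Sp and PPV, but label Se and PPV exploratory and specific to this cohort. Give the number of affected recordings and of affected women beside them.
4. Use confidence intervals that allow for repeated tracings within a woman.
5. Drop the p-value.

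The cost is a rewording of one paragraph, with no new patients or data. The downside is a more modest claim for the algorithm work, and some indication groups may be small.
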